### Intervention

The intervention group will receive the CP@home program. Community paramedics will conduct a full assessment and risk analysis of participants regarding their overall health status, quality of life, and many social determinants of health. The assessment will include some aspects of CP@clinic (e.g., overall health assessments) but will also include additional evidence-based and previously developed and validated screening assessments (neurologic, cardiac, psychiatric, and social isolation) and connect participants to existing city and community resources. Further program details are provided in Fig. 2. The aim of the CP@home intervention is to provide the participants with the appropriate resources they need based on the assessment findings and the participant’s own perceived needs. It is expected that the ongoing monitoring, identification, and introduction of community resources will improve their health and quality of life, and prevent future crises, thereby decreasing their EMS calls, ED visits, and hospital admissions.

**Fig. 2 Fig2:**
[figure not shown]
Study enrolment, intervention, and assessments. Items in brackets are completed only if appropriate and are not mandatory for all participants

Following consent, the first visit will take approximately 90 min in the participant’s home. Assessments to be completed are:Blood pressure and atrial fibrillation using a validated medical device [33]Diabetes risk using the validated Canadian Diabetes Risk (CANRISK) tool [34]○ If necessary, this will be followed up with a fasting capillary blood glucose measurementFalls risk using the Timed Up and Go test [35, 36]Neurologic assessment using the Mini-Cog Test [37]Cardiac assessment for congestive heart failure using the Rise Above Heart Failure tool from the American Heart Association [38]Respiratory assessment using the Drive4COPD tool [39]Health-related quality of life using the EQ-5D-5 L Tool [40]○ Sections used will include pain and activities of daily living, such as mobility, self-care, and usual activities.Social isolation using the Three-Item Loneliness Scale [41]Food security using a brief Hunger Screening tool [42]Income security with a tool used by primary care to identify poverty [43]

The assessments will be stored in the CP@home database using an electronic questionnaire in the REDCap platform that collects participant information, calculates risk factors, and summarizes them in a risk factor profile. The CP@home database uses an algorithm to direct participants to the appropriate health-care and community services based on their risk factor profile. If urgent care is required, action will be taken to facilitate transport to an urgent care or emergency facility. Otherwise, based on the risk assessments, referrals will be made to the appropriate resources (e.g., primary care, legal aid clinic, social worker, or local wellness programs) or health education will be provided (e.g., health promotion and appropriate use of EMS). The risk assessment of consenting participants will be sent to their family physician.

A second visit will be made to the participant 2 to 4 weeks following the initial visit for a streamlined follow-up and reassessment, which will last for 30 min. Appointments for succeeding visits are made automatically unless the participant decides not to participate anymore. The duration between appointments will vary based on the availability of participants and whether participants need more time to implement the plan and the advice agreed upon during the previous visit. The schedule for the next visit is agreed at the end of each visit. Further referrals may need to be made at this time, or referrals reinitiated.

A final visit will be made 6 to 8 weeks following the initial visit for a final evaluation of the participant’s situation. It is anticipated that the patient will be discharged from the CP@home intervention at this point. If the patient calls EMS following the third visit and they continue to meet the inclusion criteria, they will be re-entered into the CP@home intervention.

The intervention will be implemented by community paramedics from the local paramedic service who have undergone a structured training program to ensure intervention fidelity. This training encompasses 4 hours of online, interactive training modules, including case studies and observing intervention visits led by a trained paramedic.

### Primary and secondary outcome measures

The primary outcome measure will be the number of repeat EMS calls resulting in the dispatch of an ambulance. The secondary outcomes are the number of ED presentations, the number of hospital admissions in the study populations both 6 months before and after the intervention start date, the number of referrals to community services, and the number of referrals to family physicians. We will also obtain a cross-sectional description of the frequent EMS user population.

### Process evaluation measures

Process measures will assess the intervention implementation in terms of the efficiency of its delivery and compliance, and will include the number of CP@home visits (number of individual visits and number of repeat visits), program delivery (such as completion of various risk assessments), and other participant satisfaction and perception measures (such as ease of implementation, weaknesses, barriers and needed improvements).

### Data gathering procedures

The primary and secondary outcomes will be assessed over two time periods: the 6 months prior to the start of the intervention and the 6 months after the initiation of the intervention. Data will be collected from: (1) the local paramedic service databases (EMS call volumes), (2) the CP@home database, which is completed by the community paramedics (health risk assessments, quality of life, other health-related scales, and community referrals), and (3) administrative databases (ED visits, hospital admissions, and primary care visits). Administrative data will be collected pre- and post-intervention, as well as during the study. Table 1 summarizes the outcomes, data sources, and analyses. Data will be transferred from the paramedic services to the study team through a secure, encrypted virtual private network.

**Table 1 Tab1:** Summary of outcomes, data sources, and analysis

Outcome	Data source(s)	Data analysis
Primary		
Number of repeat EMS calls resulting in ambulance dispatch in the study population	Paramedic services administrative data	- Comparison between intervention and control groups after the 6-month intervention - Multi-level modeling of factors affecting outcome
Secondary		
Number of ED presentations in the study population	Hospital and ED database Paramedic services administrative data	- Comparison between intervention and control groups after the 6-month intervention - Multi-level modeling of factors affecting outcome
Number of hospital admissions in the study population	Hospital and ED database	
Number of referrals to community services (intervention group only)	CP@home database Paramedic services administrative data	- Descriptive analysis
Number of referrals to family physicians (intervention group only)	CP@home database Paramedic services administrative data	
Tertiary		
Characteristics of frequent users (baseline only)	CP@home database	- Descriptive analysis
Cost-effectiveness of CP@home	CP@home database Paramedic services administrative data	- Economic analysis
Process		
Number of CP@home visits	CP@home database	- Descriptive analysis - Thematic analysis
CP@home participant satisfaction	Self-administered survey Key informant and individual interviews of participants and paramedics	

*ED* emergency department, *EMS* emergency medical services

Physical measures (such as blood pressure), risk assessment scores, and process measures will be collected during the home visits and stored in the CP@home electronic database. Participant satisfaction will be collected through a post-intervention self-administered electronic survey and key informant interviews (KIIs). All participants will be invited to answer the self-administered electronic survey. Six intervention participants and two paramedics implementing the intervention from each site will be invited to participate in the KIIs. The surveys will be conducted during the last CP@home intervention visit. The KIIs will be conducted 6 months after the initiation of the intervention. Participants recently enrolled to the intervention and paramedics who have been implementing the program for at least 1 month in the previous 3 months will be included in the KIIs to maximize the richness of the information and minimize recall bias.

### Data analysis

An intention-to-treat analysis will compare all participants as originally allocated after randomization. This will help to avoid any bias associated with a non-random loss of participants. A sensitivity analysis will compare the results of the intention-to-treat analysis to the per-protocol analysis (which includes only participants who have completed the full program). Outcomes will be analyzed at the individual level and geographic level (e.g., by postal code or ward).

Descriptive statistics will be generated for the baseline demographics. The characteristics of the intervention and control groups will be compared. Correlations statistics will be run between variables. Multi-level modeling will be conducted to find factors predictive of the primary and secondary outcomes. Finally, a thematic analysis of the KIIs and participant feedback surveys will be completed.

Intervention fidelity will be maintained through regular monitoring of the CP@home database (by monitoring referral patterns by EMS personnel and proper use of the screening tools). The main outcomes will be analyzed after completing the participant recruitment process (pre-intervention analysis) and 6 to 9 months after completing the intervention for all participants (post-intervention data and full data analysis).

Both CP@home intervention and health-care resource utilization and costs will be collected for the economic analysis, with a focus on whether the upfront cost of the CP@home intervention is offset by other health-care cost savings [44]. Decision analytic modelling techniques will be used to project final outcomes, like life years and quality adjusted life years, from intermediate outcomes measured during the evaluation period. Our economics team has extensive experience in conducting trial-based and modelling-based evaluations aligned with the needs of health policy makers.

For the quantitative process evaluation, data will be analyzed using frequency and descriptive measures. In the qualitative process evaluation, themes and opinions will be analyzed. A within-case and cross-case analysis will be completed for themes generated to summarize the participants’ and implementers’ experiences with the program.

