**Fig. 1 Fig1:**
[figure not shown]
Study flow diagram

We have secured a waiver of consent for both intervention and control participants prior to randomization since all baseline data collected on participants will be from de-identified secondary data sources. Post-randomization, participants allocated to the intervention group can opt out from receiving the CP@home intervention and no identifiable information will be collected from this group. Those who agree to receive the CP@home intervention will be asked to provide consent since individual information will be collected as part of the intervention and evaluation process.

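### The per-protocol sensitivity analysis keeps only programme completers, a group that can form in one arm only, so it cannot show whether the intention-to-treat result is robust

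*Protocol article*

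**What the plan says.** The Data analysis section commits to ITT: "An intention-to-treat analysis will compare all participants as originally allocated after randomization". Its reason is sound: "This will help to avoid any bias associated with a non-random loss of participants". It then adds a second analysis as a check: "A sensitivity analysis will compare the results of the intention-to-treat analysis to the per-protocol analysis". The same sentence limits the set to those who finished the whole programme: "the per-protocol analysis (which includes only participants who have completed the full program". The article gives no rule by which controls enter that set.

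Other sections show how a person comes to be a completer. Under Allocation of intervention, consent is waived before randomisation; afterwards, "participants allocated to the intervention group can opt out from receiving the CP@home intervention", and "Those who agree to receive the CP@home intervention will be asked to provide consent". Controls receive usual care. Under Intervention, participants may stop between visits, and "A final visit will be made 6 to 8 weeks following the initial visit". Under Data gathering procedures, outcomes are counted over the 6 months after the intervention is initiated.

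**The concern.** Completers have accepted the programme, consented and remained available until a visit 6 to 8 weeks after the first one. Nobody in the control arm passes through that filter. Randomisation therefore does not protect the comparison, and the set is formed by the kind of non-random loss that the same paragraph gives as the reason for ITT. Completion also falls inside the outcome window: someone who deteriorates, moves or withdraws before the last visit leaves the intervention set, while a similar control stays in.

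What is at stake is interpretation. The results are intended for decision makers. A favourable completer result could be taken as confirming the ITT finding, or as rescuing a null one, with no programme effect behind it. An unfavourable one could wrongly cast doubt on a real effect.

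**Working it through.** The article gives no figure for the per-protocol analysis, so there is none to reproduce. The check asks how large a spurious difference could be.

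**Inputs from the Sample size section:** mean 5.3 calls in 6 months, SD 5.7, planned 261 per group, target difference 25%. The design difference is 0.25 × 5.3 = 1.325 calls. (The 261 serves here only as the planned arm size.)

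**Assumed, because the article does not give them:** r, the completers' untreated call rate relative to the whole arm; c, the share who complete; all controls kept as comparator; SD 5.7 in both groups.

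**1. No programme effect.** The overall arm mean stays at 5.3, so the true ITT difference is 0. The completer contrast is (r - 1) × 5.3.

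| r | Completers minus controls | Apparent change |
|---|---|---|
| 0.9 | -0.1 × 5.3 = -0.53 | -10% |
| 0.8 | -0.2 × 5.3 = -1.06 | -20% |
| 0.7 | -0.3 × 5.3 = -1.59 | -30% |

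With r = 1 there is no bias. With r above 1 the sign reverses.

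**2. Chance of a nominally significant result with no effect.** Use a two-sided z-test with SE = 5.7 × √(1/(261c) + 1/261). At c = 0.5, SE = 5.7 × √(1/130.5 + 1/261) = 0.61. The rejection rates, instead of 5%, are:

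| c | r = 0.9 | r = 0.8 | r = 0.7 |
|---|---|---|---|
| 0.3 | 11% | 30% | 58% |
| 0.5 | 14% | 41% | 74% |
| 0.7 | 16% | 49% | 82% |

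**3. A true 25% reduction among completers.** The completer mean relative to controls is r × 0.75. With r = 0.8 this is 0.60, an apparent 40% reduction. With r = 1.2 it is 0.90, an apparent 10% reduction. The estimate holds a programme effect and a selection effect that cannot be separated.

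**4. The alternative on the same example.** Controls are not offered visits, so the complier average causal effect without covariates is the ITT difference divided by intervention-arm uptake. Take c = 0.5 and r = 0.8 and, for simplicity, let completers be the only people visited. Their untreated mean is 0.8 × 5.3 = 4.24, and that of the rest is (5.3 - 0.5 × 4.24)/0.5 = 6.36.

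- No effect: ITT = 0.5 × 4.24 + 0.5 × 6.36 - 5.3 = 0, so the complier effect is 0/0.5 = 0. The completer contrast gives -1.06.
- 25% effect: ITT = 0.5 × 4.24 × 0.75 + 0.5 × 6.36 - 5.3 = -0.53, so the complier effect is -0.53/0.5 = -1.06, which is 25% of 4.24. The completer contrast gives 3.18 - 5.3 = -2.12.

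Estimate and standard error are both divided by uptake (taking uptake as known), so the test statistic is that of ITT. At 60% uptake, an ITT difference of -0.80 becomes -0.80/0.60 = -1.33, with an interval 1/0.60 = 1.67 times as wide.

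**The case against.** The strongest reply is that this is only a sensitivity analysis. ITT is the main analysis, for the right reason, and the Loss to follow-up section says that outcomes come from administrative records and do not depend on contact. That stands: nothing here touches the main estimate.

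Second, the article is condensed, and a statistical analysis plan could define the full programme, the control set and any adjustment. Those omissions are not counted here. The article does, however, state the selection rule itself, and that rule yields a biased contrast.

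Third, the illustrative biases restate their own assumptions. That is correct; they show scale, not evidence. The article gives no opt-out, completion or completer call rates, and people with greater need might be the ones who finish.

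Fourth, calls in the 6 months before the intervention are held and multi-level modelling is planned, so a stable difference could be partly adjusted for. The article does not say that the per-protocol analysis will do so, and baseline calls would not capture events between randomisation and the last visit.

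Fifth, a complier analysis without covariates gives essentially the same test as ITT, so it is not an independent check either. True; its merit is that it estimates an effect in those who accept without breaking the randomised comparison.

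From "no identifiable information will be collected from this group", said of those who opt out, a reader might also infer that their outcomes are lost and the alternative cannot be run. The wording restricts identifiable information, while the ITT commitment and the administrative outcome source cover everyone allocated.

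**Conclusion.** The point holds as a defect in a secondary analysis. The per-protocol set is selected on an event after randomisation that only one arm can experience. Read literally it leaves no comparator; set against all controls it mixes programme effect with selection. Either way it cannot serve as a check on ITT.

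Three stronger readings are tempting and not supported:

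- That the analysis measures only who finishes. It contains the programme effect as well, and is unbiased if completers resemble the arm as a whole.
- That the article specifies completers against all controls. It does not say; that comparator is inferred.
- That the bias favours the programme, or endangers the trial's conclusion. Its direction is unknown, and the ITT result is unaffected.

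The range of -0.53 to -1.59 calls under no effect, against a design difference of 1.325, rests on an assumed completer rate 10% to 30% below the mean and on all controls being kept. It shows that moderate selection could produce a difference of the size the trial was designed to detect, not that it will.

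**What to change.** Replace the completer analysis with a complier average causal effect analysis, or keep it beside one and label it exploratory and open to selection bias. Use allocation as the instrument, at least one home visit as the treatment received, and the same outcome window in both arms as the ITT analysis. One visit is preferable to full completion as the definition, because partial programmes may also have an effect. State the exclusion restriction: allocation affects calls only through receiving a visit. State also that the result estimates the effect in people who accept and is not an independent test of ITT. Report completion rates descriptively.

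The change is one of wording, to be made before outcomes are analysed. Visits are already recorded in the CP@home database (Table 1), and ITT outcomes are already planned for both arms. The price is a confidence interval wider than that of a naive completer analysis, and an assumption that the data cannot test.

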### Knowledge translation and implications

Involving key stakeholders and community partners (i.e., each region’s paramedic service, Public Health, McMaster University, and the Community Care Access Centre) in a knowledge translation and exchange process will provide opportunities to use the results when making decisions about future health programs, policies, and practices. This group of stakeholders will be involved in developing recommendations for the city council and the dissemination of the results. Dissemination includes the development of an online training tool for community paramedics regarding their expanded role in the community with an emphasis on the health promotion and non-urgent aspect of preventative health care. The educational tool developed by our team could be migrated to the platform used by the Centre for Paramedic Education and Research in Ontario. Paramedicine decision makers can share the new tool and the research results with their provincial and national EMS bodies to promote the CP@home program.

The results of this study will be presented in conferences and published in peer-reviewed and open-access journals to reach broad audiences to enhance research uptake. The potential audience to receive the results from McMaster University, paramedic services, and community partners could include decision makers, policy makers, funding bodies, and knowledge brokers. Ultimately, this program could be used to support a shift in the delivery of primary health care. Sustainability actions will involve working with relevant groups such as health-care professionals, service providers, community health support organizations focusing on older adults (e.g., Community Collaborative of the Local Health Integration Network), and decision makers from the municipal and provincial governments.

Though the setting of this study is Canada, its results could be used by other countries that are promoting CP, including members of the International Roundtable for Community Paramedicine [45]. The high frequency of EMS and ED use is a problem for many developed countries and CP has been advocated as one of the solutions to this problem.

## Discussion

Very little is known about frequent users of EMS, especially in Canada [9], but with increasing demands on the health-care system and limited resources, it is important to study this high-utilization group [3]. The CP role has been developing and expanding in recent years, and a community-based RCT of a wellness clinic model in subsidized housing showed a significant impact on EMS calls [31]. The current study will increase our understanding of the population of frequent EMS users, beyond those in subsidized housing, and the effectiveness of a home-visit CP program in reducing ambulance calls and other health-care utilization (e.g., ED visits and hospital admissions). A similar home-visit program using case managers was effective in the United Kingdom [3].

There are some key challenges to consider when implementing a community-based, pragmatic RCT in a vulnerable population, including intervention fidelity, number of eligible participants, and loss to follow-up. Each of these challenges has been addressed to minimize its potential impact.

### Ensuring that CP@home is properly implemented

Training modules will be developed to ensure that implementers conduct the program properly. Fidelity checks will help in assessing the implementation of the program. Regular quality assurance assessments of the entered data will also be done to monitor the implementation of the program and data collection. To ensure the most accurate results, individuals living in long-term care facilities and individuals currently involved in a paramedic home-visit program or other paramedic-led frequent user intervention will be excluded from the analysis. Existing services and programs in the community during the duration of the CP@home study will be noted and accounted for in the analyses due to the possibility of co-intervention.

